### Specific objectives

1. Evaluate the effectiveness of the integrated Infectious Disease Training in preparing mid-level practitioners to perform key clinical tasks corresponding to infectious disease competencies at acceptable standard
2. Evaluate the effectiveness of on-site support services (OSS) in improving clinic performance
3. Estimate the cost-effectiveness of site support services
4. Compare two methods for estimating cost-effectiveness: a) economic modeling in which effectiveness is measured by original data on performance indicators at 36 sites and published estimates of the effect of the performance indicators on Disability Adjusted Life Years (DALYS), and b) estimates in which effectiveness is measured original verbal autopsy data on mortality among children five years or less.
5. Evaluate the effectiveness of bi-monthly OSS for six months on clinical performance at Phase 1 sites after monthly OSS for nine months during Phase 1.

##

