For specific objective 4, cost-effectiveness will be estimated with two methods. The first method is a model that combines original data on the performance indicators described in Table 1 at 36 sites and the cost of the capacity-building programs with published estimates of the cost of treatment and DALYs saved. The second method is based on original data on mortality of children under five years as described in Section 3.4 below, instead of performance indicators and DALYs. In other words, the denominator of the incremental cost effectiveness ratio will be measured two ways: economic modeling in which effectiveness is measured by original data on performance indicators and published estimates of the effect of the performance indicators on DALYS, and b) estimates in which effectiveness is measured with original verbal autopsy data on mortality.

The first method was proposed by Mason et. al. to estimate “policy-cost-effectiveness.”[[19]](#endnote-20) Their method grew out of observation that many cost-effective treatments were not adopted by providers. For example, the cost-effectiveness of co-trimoxazole prophalaxis is well established. Pitter et. al estimated that providing it to all HIV-infected people is cost-saving ($2.5 per person year) and providing it only to people in WHO clinical stages 2, 3, and 4 cost $22.23 per DALY gained relative to no prophalaxis.[[20]](#endnote-21) Yazdanpanah et.al. estimated that providing it to people in WHO clinical stages 2, 3, and 4 cost $150 per life year saved relative to no prophalaxis.[[21]](#endnote-22) This evaluation does not seek to replicate the cost-effectiveness analysis of this treatment. It evaluates the cost-effectiveness of a capacity-building intervention that promotes the adoption of the treatment at health facilities.

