The health sector perspective includes the time of health professionals. Estimates of the cost of the capacity-building intervention will include the opportunity cost of time when health professionals are away from the site at IDI and on-site participating in OSS. District and facility personnel records will be used to identify the profession of participants and the average salary for that profession will be used in the cost estimates.

Original data on the costs of treatments will also be collected, including staff, drugs and laboratory tests. The cost of staff time will be calculated as the opportunity cost of time as described above. The cost of drugs and laboratory tests will include: HIV test kits, cotrimoxazole, first line ART, TB drugs, coartem, reagents for laboratory tests. Data on the quantities of the drugs and reagents reported on stock cards will be multiplied by the MOH unit price.

The published estimates of effectiveness of treatment (e.g. A3 in Table 2) will be measured in life DALYs or life years. These effectiveness measures serve as a common denominator so that costs and effects can be added across treatments. Weaver et. al. used this method to estimate the cost effectiveness of an influenza and pneumococcal vaccination program and found that a combined program was more cost-effective than a program that focused on a single vaccine.[[31]](#endnote-32)This feature is potentially the key to showing that OSS, which might appear expensive for a vertical program, would become cost-effective in the context of an integrated infectious disease capacity-building program.

A cost analysis will be conducted from the providers’ prospective, and focus on workload. Some treatments require spending more time with each patient, which may not be feasible for clinicians who see 80 or more patients per day. The treatment would be more attractive to clinicians if additional staff were trained to provide it, so that the patient load is shared among more staff. It would also be more attractive to clinicians if it reduced the number of visits per episode of illness.

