### 3.4.2 Design

For the second cost-effectiveness analysis, an alternative measure of effectiveness will be years of life saved. Population-level data is the only valid way to directly measure the effect of the intervention on health outcomes.

It is expected that the capacity-building and quality improvement interventions will reduce mortality by improving the emergency triage and treatment of patients and improving the quality of care for infectious diseases. The Uganda Child Verbal Autopsy Study showed that 75% of children who died received care from a government or private hospital or health center.[[35]](#endnote-36) Given that these children had access to care, it may be possible to save their lives by improving the quality of that care.

When the quality of care improves, utilization of a health facility increases.[[36]](#endnote-37) [[37]](#endnote-38) If the quality of care improves at the Phase 1 sites, they are likely to attract more patients including sicker patients. Paradoxically, as the quality improves the mortality of patients at the facility may increase, because the volume of patients and case complexity increases. Population-level data at the Phase 1 sites would reveal that population-level mortality had decreased because more people are seeking care, even if facility-level mortality increased.

UBOS proposed estimating population-level mortality with a two-part sampling method that builds on recent advances in the Demographic Surveillance Systems in which representatives of local council members at the parish level provide information about recent deaths. Although vital records systems may not be reliable in many African countries, there is a policy in Uganda for citizens to report births and deaths to the local council members. The information is more reliable in rural parishes than urban.

In the first part, the local council member directs the interviewers to households where there is a “high index of suspicion” that a death of a child U5 has occurred. To ensure completeness, a listing of households in each enumeration area (EA) would be created from interviews with all households in collaboration with the local council member. The listing includes an identification number and location for each household, whether or not a death occurred within the household in the last 3 years, and if yes, the age of the person at the time of his/her death.

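### The unit of effect is left open (DALYs or life years) where effects are to be summed across treatments, and hypothesis 4 compares two cost-effectiveness ratios in different units

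*Protocol*

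**What the plan says.** For the modelled cost-effectiveness analysis, section 3.3.1 states that the published effects of treatment "will be measured in life DALYs or life years. These effectiveness measures serve as a common denominator so that costs and effects can be added"; the addition runs over the treatments in the programme. It presents this summation as what might make OSS cost-effective as an integrated programme when it looks expensive for a single disease. The text does not choose a unit and gives no rule for sources that report only the other one.

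Elsewhere the modelled method is described in DALYs alone. Specific objective 4 names DALYs as its measure. An earlier paragraph of 3.3.1 combines site data "with published estimates of the cost of treatment and DALYs saved". Table 2, which section 3.3.2 makes the template for the analysis, is in DALYs throughout.

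For cotrimoxazole, Table 3 lists two example sources. Section 3.3.1 reports that, for WHO stages 2 to 4, one found that prophylaxis "cost $22.23 per DALY gained relative to no prophalaxis" and the other that it "cost $150 per life year saved relative to no prophalaxis".

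For the mortality-based method, 3.3.1 says that under-five mortality replaces performance indicators and DALYs. Section 3.4.1 divides incremental cost by the difference-in-difference in the mortality rate. Section 3.4.2 says instead that "an alternative measure of effectiveness will be years of life saved". Hypothesis 4b predicts that the mortality-based ratio will be lower than the modelled one.

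**The concern.** DALYs averted and life years saved are different quantities. A saved year lived with disability weight w counts as one life year but as only 1 − w of a DALY averted, and life years give no credit for non-fatal illness avoided. Effects can be added only when every term is in the same unit. With the unit open and both kinds of source among the examples, the summed benefit could depend on which paper is picked for each treatment. Hypothesis 3, on whether OSS is cost-effective, draws on that sum.

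Hypothesis 4 raises a separate problem. It is a directional statement about two ratios, and it can be read only if their denominators are on one scale. As written they are not, so a finding that one ratio is lower would partly reflect the unit.

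**Working it through.** **1. The protocol's own example.** Table 2 gives DALYs gained = 0.13430 − 0.06861 = 0.06569, shown as 0.0657. Incremental costs are 56.69 − 49.19 = $7.50 for classroom training and 156.69 − 49.19 = $107.50 for classroom training plus OSS. Benefits are 0.0657 × 0.05 = 0.0033 and 0.0657 × 0.9 = 0.0591. The ratios are 7.50 / 0.0033 = $2,273 and 107.50 / 0.0591 = $1,819, as stated (2,283 and 1,818 without rounding the benefits). The example covers one treatment in one unit, so it contains no mixing and does not show how treatments would be summed.

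**2. Three ways to read the sentence in 3.3.1.**
- DALYs for all treatments: the sum is valid and agrees with objective 4, but the mention of life years is then wrong.
- Life years for all treatments: the sum is valid, but it contradicts objective 4, the rest of 3.3.1 and Table 2.
- The unit varies by source: the sum has no single scale.

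On each reading the wording needs correcting.

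**3. What mixing would do, if it occurred.** Let s be the share of the summed effect that is entered in life years, and k the DALYs averted per life year saved in that share. With the same total cost,

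mixed ratio / all-DALY ratio = (1 − s) + s·k.

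The protocol gives neither s nor k. Under assumed values:
- s = 0.75, k = 0.8: 0.25 + 0.60 = 0.85
- s = 0.5, k = 0.8: 0.5 + 0.4 = 0.90
- s = 0.5, k = 1.5: 0.5 + 0.75 = 1.25
- s = 0.75, k = 2: 0.25 + 1.5 = 1.75

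The error vanishes only at k = 1. Values of k below 1 arise when the years saved are lived with disability, and values above 1 when much of the benefit is non-fatal. Both signs are possible.

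**4. The cotrimoxazole pair.** 150 / 22.23 = 6.7. The two figures come from different studies in different countries, so this is not a conversion factor between units.

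**5. Hypothesis 4.** Let C be the incremental cost, D the deaths averted, L the years of life lost per death, and N the non-fatal DALYs averted.
- Modelled method (objective 4): C divided by DALYs, that is C / (L·D + N).
- Section 3.4.2: C divided by years of life saved, that is C / (L·D).
- Section 3.4.1: C divided by a difference in rates. Once multiplied by the child-years at risk this becomes C / D.

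For the same deaths, the ratio per death is L times the ratio per year of life, so the choice between 3.4.1 and 3.4.2 alone rescales the mortality-based ratio by L. With the same L and discounting, the ratio per year of life saved is 1 + N/(L·D) times the ratio per DALY. With a different L or different discounting it could fall on either side. The protocol gives no L, N or discount rate, so the size of the unit effect cannot be computed. That the units differ follows directly from the wording.

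**The case against.** The fairest defence is that the sentence offers a choice of one unit for the whole analysis, and that everything else about the modelled method points to DALYs. On that view this is loose wording and nothing will be mixed. Table 3 gives examples only, the worked calculation uses only the DALY source, and the protocol does not state the unit of the sources for the other treatments. Weights and discounting are commonly left to the statistical analysis plan, which is not at hand. For hypothesis 4, comparing two measures of effect is the declared purpose. The methods also differ in population: children under five within 5 km of a site, against patients of all the modelled treatments, including ART and TB. Aligning units would not by itself make the ratios comparable.

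Much of this stands, and it rules out three stronger conclusions that a reader might draw.
- That the protocol will add DALYs to life years. It permits this but does not say so.
- That the combined ratio fails against a stated cost-per-DALY benchmark. The analysis follows WHO-CHOICE and hypothesis 3b refers to interventions that WHO recommends, but no such threshold is stated.
- That the 6.7-fold gap measures the effect of the unit. Study and setting differ as well.

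Two things are not answered. The sentence in 3.3.1 still conflicts with objective 4. And a deliberate comparison of two methods still needs a common scale when the hypothesis says which ratio is lower. The units would coincide only if 3.3.1 meant life years throughout and 3.4.2 overrode 3.4.1, which objective 4 excludes.

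**Conclusion.** The point holds in two parts. First, 3.3.1 leaves the unit of effect open while planning to sum effects, in conflict with the DALY wording elsewhere and with sources in both units among its examples. Mixing would leave the combined ratio without a single scale. Its size and sign cannot be settled from the documents, and the range of 0.85 to 1.75 times the all-DALY ratio is an illustration under assumed shares and conversions, not an estimate. Second, with objective 4 taken as written, hypothesis 4 sets a ratio per DALY against one per year of life saved or per unit of mortality difference, and sections 3.4.1 and 3.4.2 do not agree on which. This part rests on no assumed figure. Both should be corrected, although they concern the economic analysis and leave the randomized comparison of facility performance untouched.

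**What to change.** In 3.3.1, name DALYs averted as the single unit for every term of the sum, in line with objective 4. Use the DALY source where both kinds exist, as for cotrimoxazole. Where a treatment has only a life-year estimate, either convert it with a stated disability weight and vary that weight in a one-way sensitivity analysis, or report the treatment outside the sum.

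In 3.4.1 and 3.4.2, name one and the same mortality denominator. Before testing hypothesis 4, convert deaths averted to years of life lost averted, using the same life expectancy and discounting as the modelled DALYs. Compare this with the fatal component of the modelled DALYs only where the published sources report that component. State that the two methods also cover different populations, so that a remaining difference is not put down to method alone.

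The cost is wording and a small conversion step, without new data. The downside is that converted terms rely on assumed weights, which is why the sensitivity analysis belongs with them. Some sources may not separate fatal from non-fatal effects, and there the narrower comparison cannot be made.

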### 3.3.2 Design

Hypothesis 2 will be tested with comparisons of the mean difference (effect size) in the performance indicators described above between Phase 1 and Phase 2 sites. The difference will be calculated between baseline and month nine. The primary analysis will be a regression of clinic-level data where the performance indicator after nine months is the dependent variable. The independent variables will include a dummy variable for whether the site was in Phase 1 or Phase 2 sample, and the indicator at baseline.

Other independent variables will include process indicators that describe the health system factors affecting performance at the facility level as shown in Table 1. Although the training program will not focus on these indicators, we will attempt to control for them in our analyses. MOH and URC have developed a set of indicators for HIV/AIDS services that are tracked during their monthly visits that will be extended to other infectious diseases. Examples include availability of HIV test kits and antiretroviral drugs, and presence of working laboratory equipment. Process measures for the laboratory are routine baseline and end-of-intervention assessments of laboratory characteristics and the performance of individual laboratory professionals at all sites. Data on skills of laboratory professionals will be collected as individual assessments as part of the OSS break-out sessions.

URC recently introduced a measure of employee engagement as a CQI process indicator that will also be collected for IDCAP.[[32]](#endnote-33) The measure is a 16-item questionnaire with questions such: “I know what is expected of me at work” and a likert scale with five response categories (e.g. strongly disagree). Staff will be asked to complete an employee engagement questionnaire three times during the on-site support: 1) at the beginning of phase 1, 2) end of phase 1, and end of phase 2. The employee engagement questionnaire will be administered by the data technicians during their quarterly visits all IDCAP sites.

The cost-effectiveness analysis based on the Mason et. al. model will be calculated as demonstrated in Table 2. The analysis will have two types of sensitivity analysis. One-way sensitivity analyses will be used to examine the magnitude of the change in the cost effectiveness ratio from varying specific parameters. For key parameters, such as the effectiveness of the intervention, a *quasi*-confidence interval will be calculated based on the confidence intervals of parameter for the dummy variable for whether or not the site was in Phase 1 or Phase 2.**[[33]](#endnote-34)** The cost of the intervention will not be included, because it will be deterministic. These calculations will also include the cost and effectiveness of treatments based on confidence intervals of those parameters in the literature.

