| **A. Pitter et.al. estimates** |  |  | |
| A1. Net treatment cost | $49.19 | $46.69 | |
| A2. Number of DALYS lost | 0.13430 | 0.06861 | |
| A3. Incremental benefit, i.e.DALYS gained |  | 0.0657 = 0.13430 - 0.06861 | |
| A4. Incremental cost |  | -$2.5 = $46.69 - $49.19 | |
| A5. Incremental cost-effectiveness ratio |  | Cost saving | |
| **B. Estimates with capacity-building** |  | **Classroom training** | **Classroom training plus OSS** |
| B1. Training cost |  | $10 | $110 |
| B2. Net program cost with training |  | $56.69  = $46.69 + 10 | $156.69  = $46.69 + $110 |
| B3. Effectiveness of training program at changing provider behavior |  | 5% | 90% |
| B4. Incremental benefit, i.e. DALYS gained |  | 0.0033  = 0.0657 * 0.05 | 0.0591  = 0.0657 * 0.9 |
| B5. Incremental cost |  | $7.50 | $107.50 |
| B6. Incremental cost-effectiveness ratio |  | $2273  = $7.50 / 0.0033 | $1819  = $107.5 / 0.0591 |

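### Table 2, the template for the model-based cost-effectiveness analysis, scales the DALY gain by uptake but carries the treatment-cost difference at full uptake

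*Protocol*

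**What the plan says.** Section 3.3.1 describes a model that joins the cost and effectiveness of the capacity-building programme to published estimates of treatment cost and DALYs, and works an example for cotrimoxazole prophylaxis in Table 2. Section 3.3.2 then makes that example the method: the analysis "will be calculated as demonstrated in Table 2".

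Part A of the table gives the published figures, with no prophylaxis first and prophylaxis for all HIV-infected people second: "A1. Net treatment cost | $49.19 | $46.69". The DALY gain (A3) is "0.0657 = 0.13430 - 0.06861", and the incremental cost (A4) is a saving, shown as minus "2.5 = $46.69 - $49.19".

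Part B adds training: "B1. Training cost | | $10 | $110" for classroom training and for classroom training plus OSS. The row "B3. Effectiveness of training program at changing provider behavior" is 5% and 90%. Row B4 multiplies the DALY gain by that percentage. The row "B2. Net program cost with training" adds training cost to the whole $46.69 in both columns. Row B5 is then $7.50 and $107.50, and row B6 is $2273 and $1819 per DALY, both relative to no prophylaxis.

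**The concern.** A patient whose provider does not change practice gains no DALYs, and row B4 respects this. The same patient also stays at the no-prophylaxis cost of $49.19, and rows B2 and B5 do not respect that: they give every patient the treated cost of $46.69 even when only 5% are treated.

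This ratio serves Hypothesis 3 (whether OSS is cost-effective) and the modelling method in specific objective 4. Section 3.3.1 also plans to add costs and effects across treatments, so the rule would enter every treatment whose net cost is not zero. Section 3.3.2 varies effectiveness in sensitivity analysis and bases a quasi-confidence interval on the Phase 1/Phase 2 coefficient. Under Table 2's rule the treatment cost stays fixed while effectiveness moves, so that interval is affected too.

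**Working it through.** **Inputs (all from Table 2).** A3 = 0.0657 DALYs. A4 = -$2.50. B1 = $10 (classroom) and $110 (classroom plus OSS). B3 = 0.05 and 0.90.

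**1. Reproduce the printed figures.** Table 2's rule is (B1 + A4) / (B3 x A3), with B4 rounded to four decimals.
- Classroom: (10 - 2.50) / 0.0033 = 7.50 / 0.0033 = $2,273.
- OSS: (110 - 2.50) / 0.0591 = 107.50 / 0.0591 = $1,819.

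Both agree with row B6. The divisions are right; the fault is in the structure of the formula.

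**2. Apply uptake to cost as well.** Expected cost per patient at uptake B3 is B1 + B3 x 46.69 + (1 - B3) x 49.19. Subtracting 49.19 leaves B1 + B3 x A4.
- Classroom: 10 + 0.05 x (-2.50) = $9.875.
- OSS: 110 + 0.90 x (-2.50) = $107.75.

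**3. Recalculate the ratios.**

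| | As printed | Consistent, rounded B4 | Table 2's rule, unrounded B4 | Consistent, unrounded B4 | Change |
|---|---|---|---|---|---|
| Classroom | $2,273 | $2,992 | $2,283 | $3,006 | 9.875/7.50 - 1 = +32% |
| Classroom plus OSS | $1,819 | $1,823 | $1,818 | $1,822 | 107.75/107.50 - 1 = +0.2% |

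**4. Locate the bias.** The consistent ratio separates into B1/(B3 x A3) + A4/A3. Table 2's rule gives B1/(B3 x A3) + A4/(B3 x A3). The training part is the same; the treatment part is multiplied by 1/B3, which is 20 at 5% uptake and 1.11 at 90%. The two rules agree only if uptake is 100% or A4 is zero. When A4 is a saving, as here, the saving is over-credited and the ratio is too low. When A4 is positive, the cost is overcharged and the ratio is too high.

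**5. OSS against classroom training (not printed in Table 2).** Under Table 2's rule the treatment cost cancels: (107.50 - 7.50) / (0.0591 - 0.0033) = 100 / 0.0558 = $1,792. The additional patients treated under OSS add DALYs but no treatment cost or saving. Consistently, it is (107.75 - 9.875) / 0.0558 = 97.875 / 0.0558 = $1,754, about 2% lower.

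**6. Illustration with a positive net treatment cost.** Assume A4 = +$50, a figure that is not in the protocol, with other inputs unchanged and B4 unrounded (A3 = 0.13430 - 0.06861 = 0.06569).
- Classroom: Table 2's rule gives 60 / 0.0032845 = $18,268; the consistent rule gives 12.50 / 0.0032845 = $3,806.
- OSS: 160 / 0.059121 = $2,706, against 155 / 0.059121 = $2,622, about 3% apart.

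The distortion falls mainly on the low-uptake programme, so with a positive net cost it makes OSS look better relative to classroom training.

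**The case against.** **The table is only an example.** It is headed as sample calculations, section 3.3.1 calls Part B hypothetical, and the conclusion drawn from it (OSS ahead of classroom training) is unchanged. This limits what the printed figures mean. It does not rescue the formula, because section 3.3.2 adopts the table as the method.

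**Treatment costs will be observed.** Section 3.3.1 plans stock-card quantities multiplied by the Ministry of Health unit price, and these would reflect actual uptake. That would be a sound remedy, but nothing links these data to B2 or B5. The same section describes the model as using published treatment costs, and section 3.3.2 takes treatment cost in the sensitivity analysis from the literature.

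**B3 may be a count.** The text with Table 3 says the number of patients treated will supply B3. A count would have to be applied to cost as well as to benefit, and the protocol does not show how. This point supports a clarification; it does not repair Table 2.

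**B1 could be a cost per treated patient.** Then the DALY gain should not be multiplied by B3 either, so the inconsistency remains.

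**Stronger readings.** A reader might infer that every ratio in the analysis will be materially wrong, or that OSS could be made to look unaffordable. The protocol's figures show neither. One could pair the 18-point design difference in section 3.3.4 with the $22.23 per DALY cited in section 3.3.1 and report a treatment part of 22.23 / 0.18 = $123.50. But the 18 points concern malaria testing and the $22.23 concerns cotrimoxazole, and that comparison leaves out training cost. With Table 2's $110 and 0.0657 DALYs, assumed to apply here too, the training part at 18 points is 110 / (0.18 x 0.0657), about $9,300. The excess of 123.50 - 22.23, about $101, is then about 1% of the ratio.

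**Conclusion.** The point stands as an error in a stated formula: Table 2 applies uptake to the benefit and not to the treatment cost, and no other part of the protocol corrects it. In the printed example it understates the classroom ratio materially and the OSS ratio negligibly, and leaves the ranking as it is.

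How much it matters in the real analysis depends on uptake and on net treatment cost relative to training cost. The 5% and 90% in Table 2 are hypothetical, and the protocol gives no net cost per patient for the other treatments in Table 3, so no overall size can be stated. What follows by algebra alone is the 1/B3 factor in the treatment part, the loss of treatment cost from an OSS-against-classroom comparison, and the effect on any sensitivity analysis that varies B3. The recalculation assumes that B1 is a cost per patient in the programme and that patients whose provider does not change keep the no-prophylaxis cost and DALYs. Row B4 already makes the second assumption for DALYs.

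**What to change.** - In Table 2, set B5 = B1 + B3 x A4, so that the ratio is B1/(B3 x A3) + A4/A3. Redefine B2 to match: 49.19 + 9.875 = $59.065 for classroom training and 49.19 + 107.75 = $156.94 for OSS.
- Recalculate B6 with one rounding rule: $2,992 and $1,823 with B4 as printed, or $3,006 and $1,822 unrounded.
- Apply the same formula to each treatment in Table 3 and in the sensitivity analyses, so that treatment cost moves with effectiveness.
- Where the trial's own treatment-cost data replace published costs, state that they enter as observed cost at observed uptake and are not scaled by B3 again.
- State how the patient counts in Table 3 are turned into B3.

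The cost is one corrected table and a few sentences. Design, sample size and data collection are unaffected.
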